**Timing of Assessments:**

- Items 1–5: Screening / registration, Day 1 of the comparative period, end (or discontinuation) of comparative period, and end of continuous period.
- Items 6–11: End (or discontinuation) of comparative period, and end of continuous period.

**Rationale for Endpoint Selection:**

- Items 1–3 (excluding localized NRS): internationally standardized measures for QOL in oral mucositis.
- *Localized NRS*: captures pain limited to the specific mucosal site.
- Item 4: assesses overall oral mucositis occurrence.
- Items 5–9: necessary to evaluate efficacy of the investigational device.
- Item 10: required for assessing technical feasibility of device application.
- Item 11: necessary for evaluating patient acceptability and continued use.

**(3) Evaluations Not Required for Control Group**

For participants assigned to the control group during the comparative period, the following assessments are not required (but are required during the continuous period, if conducted):

- Technical performance evaluation
- Patient preference for investigational treatment
- Device malfunction assessment
- Causality assessment of adverse events related to device use

## **7. Target Sample Size and Rationale**

**Target sample size:** 154 participants

- Intervention group (standard care + investigational device): 77
- Control group (standard care only): 77

### **Rationale:**

In the exploratory trial, the proportion of improvement in oral mucositis at Day 15 was 58.3% (7/12) in the intervention group and 0.0% (0/6) in the control group.

Considering the small control group size in the exploratory study, the uncertainty of the estimated effect, and the allowance of concomitant use of existing mucosal protectants (which may enhance control group outcomes), as well as inclusion of *prevention of onset* as an endpoint in this confirmatory study, the expected improvement rates were conservatively assumed as 50% in the intervention group and 25% in the control group.

With a two-sided significance level of 5% and 90% power using Pearson's chi-square test, 77 participants per group (total n=154) are required.

Based on previous accrual rates ( $\geq 10$  participants per year per site), this total sample size is feasible within the study period across the participating centers.

## **8. Data Compilation and Statistical Analysis**

### **(1) Analysis Populations**

Three analysis populations will be defined:

#### **1. Full Analysis Set (FAS):**

All participants who were randomized, received treatment, and had at least one efficacy assessment (primary or secondary).

#### **2. Modified Full Analysis Set (mFAS):**

Subset of the FAS excluding participants with major protocol deviations affecting efficacy evaluation. Analyses using mFAS will be conducted as needed.

#### **3. Safety Analysis Set (SAF):**

All participants who were registered and received at least one treatment.

### **(2) Statistical Methods**

## **1) Analysis of Demographic and Baseline Characteristics**

Major background variables and related characteristics will be summarized by group.

For quantitative variables, summary statistics (n, mean, standard deviation, standard error, minimum, maximum, and quartiles) will be calculated.

For categorical variables, frequencies and percentages will be tabulated.

## **2) Analysis of the Primary Endpoint**

### **Primary Endpoint:**

Oral mucositis severity based on CTCAE v3.0 subcriteria during the comparative period.

### **Statistical Analysis:**

- Cross-tabulation of each CTCAE grade at Day 1 versus subsequent evaluation points by treatment group.
- Estimation of the frequency, percentage, and two-sided 95% confidence interval (CI) of subjects achieving *prevention of onset* or *pain improvement* at each timepoint.
- Comparison between groups using Pearson's chi-square test (two-sided,  $\alpha = 0.05$ ).
- Estimation of the between-group difference with a two-sided 95% CI.

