### **4. Method of Randomization**

Before the start of the study, the Randomization Supervisor will prepare a reproducible randomization table using computer-generated random numbers.

A stratified block randomization method will be applied, stratified by study site planned to conduct the comparative period.

The allocation ratio between the intervention and control groups will be **1:1**, based on the planned total sample size.

As this is an open-label study, detailed algorithmic parameters of the randomization will not be described in this protocol to prevent predictability of assignment and potential selection bias. Instead, they are specified in a separate *Randomization Specification Document*, which will remain confidential until all participants have been assigned.

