#### **Statistical Methods:**

- For items (1)–(2), analyses identical to those for the primary endpoint will be applied.
- For item (5), subgroup analyses by chemotherapy regimen will be performed similarly.
- For other items:
  - Categorical data: same as primary analysis (frequencies, percentages, chi-square).
  - Continuous data: summary statistics (as above), estimation of intergroup differences and 95% CIs, and use of two-sample Wilcoxon or two-sample t-tests depending on distribution.
  - Analyses will also be performed on *change from Day 1*.
  - *Pain NRS* will be analyzed both as a continuous variable and as categorical (0 = none, 1–3 = mild, 4–6 = moderate, 7–10 = severe).
  - For participants with multiple affected sites, the worst score per period will be used.

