## **5) Significance Level and Confidence Coefficient**

- Significance level: 5% (two-sided)
- Confidence coefficient: 95% (two-sided)

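### The primary chi-square test leaves out the site strata and Day-1 mucositis status; it is valid and adequately powered, but a stratified test would match the design and use the data better

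*Protocol*

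**What the plan says.** **Allocation.** Protocol Section 4(7), Method of Randomization, uses 1:1 block randomisation "stratified by study site planned to conduct the comparative period". Section 3 gives four institutions. No other stratification factor is named.

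**Success.** The definitions in Section 8(2)2) depend on the Day-1 state of the target site. A participant without mucositis there succeeds by still having none. A participant at Grade 1, 2 or 3 succeeds only if the grade falls or the lesion clears. Eligibility (Section 10) requires tooth-mucosa contact, not mucositis, so both kinds of participant can enrol.

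**Primary test.** Section 8(2)2) states "Comparison between groups using Pearson's chi-square test", two-sided at 5%, plus a between-group difference with a 95% CI. Neither site nor Day-1 status enters either of them. Section 7 sizes the trial for the same test: "With a two-sided significance level of 5% and 90% power using Pearson's chi-square test, 77 participants per group (total n=154) are required", with success rates "conservatively assumed as 50% in the intervention group and 25% in the control group".

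**The concern.** An analysis normally reflects the factor used to stratify randomisation. Here a second variable, Day-1 mucositis status, decides which success criterion applies to a participant. If success is much more common in one baseline group than in the other, pooling leaves that explained variation in the error term. A chance imbalance in baseline status between arms can then move the crude difference.

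The protocol hints at such a gap without quantifying it. In the exploratory trial 0 of 6 controls improved (Section 7). Section 3 puts mucositis at about 40% of chemotherapy patients, so many controls who start free of it may stay free. Section 7 also lists the inclusion of prevention of onset among its reasons for the assumed rates.

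What is at stake is precision and agreement between design and analysis, not the validity of the result.

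**Working it through.** **Inputs from the protocol:** 50% versus 25% success, two-sided 5%, 90% power, 77 per group (Section 7); site as the only stratum (Section 4(7)); four sites (Section 3).

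**Assumptions, not in the protocol:** the share of participants free of mucositis on Day 1, success rates within baseline strata, and success rates by site. They are varied below with the overall rates held at 50% and 25%.

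**1. The planned figure.** With mean rate 0.375:

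n = [1.960·√(2·0.375·0.625) + 1.282·√(0.5·0.5 + 0.25·0.75)]² / 0.25² = 76.7, so 77 per group. The protocol's figure reproduces.

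Power at 77: SE under the null = √(2·0.375·0.625/77) = 0.0780; SE under the alternative = √((0.25 + 0.1875)/77) = 0.0754; Φ[(0.25 − 1.96·0.0780)/0.0754] = 90.1%. No test could add more than 100 − 90.1 = 9.9 points at these rates.

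**2. CMH by baseline status.** Use the same formula with within-stratum variances: replace 2p̄(1−p̄) by Σ w·2p̄ₛ(1−p̄ₛ), and the alternative variance likewise, where w is the stratum share. For half free of mucositis and a constant 25-point effect:

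| Control success, free / affected | Gap | CMH power | Gain |
|---|---|---|---|
| 25% / 25% | 0 | 90.1% | 0 |
| 30% / 20% | 10 | 90.4% | 0.3 |
| 35% / 15% | 20 | 91.4% | 1.2 |
| 40% / 10% | 30 | 92.9% | 2.7 |
| 45% / 5% | 40 | 94.8% | 4.7 |
| 50% / 0% | 50 | 96.9% | 6.8 |

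Example for the 30-point gap: the SEs fall to 0.0742 and 0.0714, and Φ[(0.25 − 1.96·0.0742)/0.0714] = 92.9%.

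With 30%, 70% or 80% free of mucositis, the gain is 0 to 5.9 points. With a constant odds ratio it reaches 9.0 points, but only at control rates of 48% and 2%. At control rates of 60% and 0% it is 8.5. Simulation (40,000 trials per scenario) agrees with the formula to within about 1 point.

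**3. CMH by site only, four equal sites.** Power is 90.1% with equal site rates and 91.7% with control rates of 10/20/30/40%, a gain of 0 to 1.6 points. With equal rates, simulation gave 90.5% for chi-square and 89.5% for CMH, a loss of about 1 point. With sites balanced between arms (100,000 trials) the loss was smaller, 90.5% versus 90.3%.

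**4. Type I error, sites balanced between arms.** Chi-square: 5.0% with similar sites, 4.3% with control rates of 10/20/30/40%. CMH: 4.9% to 5.0%.

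**5. Chance imbalance in baseline status.** With half free of mucositis, the SD of the between-arm difference in that share is √(2·0.25/77) = 8.1 points. A 1.96-SD imbalance is 15.8 points. Multiplied by a control-rate gap of 0.4 to 0.5, it shifts the crude difference by about 6 to 8 points, against a planned 25.

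**6. Smaller true effect.** At 45% versus 25% overall, chi-square power is 74.4%. With half free of mucositis, CMH gives 78.8%, 82.4% and 87.1% at gaps of 30, 40 and 50: gains of 4.4, 8.0 and 12.7 points.

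**The case against.** The strongest reply is that nothing is wrong. Randomisation makes the unadjusted test valid, chance imbalance is already covered by the 5% error rate, and planned test and planned N agree. That stands. It is also true that the gain depends on figures the protocol does not give. Day 1 precedes that cycle's chemotherapy and mucositis is not required for entry, so most participants could start without it, and the gain would then shrink.

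It could further be said that stratified analyses belong in the statistical analysis plan. Supportive ones often do, but the protocol itself names the primary test, so changing it is a change to stated text.

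Two wider criticisms are tempting and not supported. A reader might infer that pooling conceals whether any benefit is prevention or improvement. Section 8(2)2) already plans a cross-tabulation of Day-1 grade against later grade by arm, which shows both; what it lacks is a stratum-specific effect estimate. A reader might also extend the point to the continuous secondary endpoints, where the protocol plans "use of two-sample Wilcoxon or two-sample t-tests depending on distribution". Section 8(2)3) already analyses change from Day 1, and replacing a rank test by covariance analysis is debatable for single ordinal items and tablet counts. Neither belongs to this point.

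**Conclusion.** The point holds as an improvement in efficiency and consistency. The primary test leaves out the randomisation stratum and a baseline variable that determines how success is judged. It remains valid, keeps its stated 90% power and does not inflate type I error.

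A reader might infer that the plan wastes more than 10 points of power. At the protocol's own rates that is impossible, since only 9.9 points remain. Gains of 10 points or more need both a true effect smaller than planned and a control-rate gap of about 50 points. For example, control 60% and 10% against device 78% and 28%, in equal strata, means 35% versus 53% overall, an 18-point effect; power is then 62% for chi-square and 75% for CMH. The protocol supports neither condition.

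At the planned rates the expected gain is about 0 to 3 points for gaps up to 30, about 5 to 7 for gaps of 40 to 50, up to 9 in extreme cases, and under 2 for site alone. All of these rest on an assumed baseline mix and assumed stratum rates.

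**What to change.** In Section 8(2)2), make the primary test a CMH test stratified by site and Day-1 mucositis at the target site (none versus Grade 1 or higher). Give the Mantel-Haenszel common risk difference with its 95% CI, and report the effect within each baseline stratum. Keep the Pearson chi-square as supportive.

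The target of 154 can stay. Section 7 should then say that the sample size was calculated for the unstratified test.

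The cost is wording, with no new data, since site and Day-1 grade are already collected. Four sites by two baseline states give eight strata, about 19 participants each on average (154/8). The statistical downside is a loss of about 1 point of power if the strata turn out not to be prognostic. The change should be made before any comparative results are seen, because the trial is open-label.

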### **Definitions:**

- *Prevention of onset*: Absence of mucositis at the target site before and after the evaluation period ("none → none").
- *Pain improvement*: CTCAE v3.0 oral mucositis grade at baseline "Grade 1/2/3" → lower grade or "none" at the target site.

## **3) Analysis of Secondary Endpoints**

### **Secondary Endpoints:**

1. Same as the primary endpoint during the continuous period.
2. Oral mucositis and oral pain grades (CTCAE v5.0 / MedDRA/J v25.1).
3. QOL: PRO-CTCAE v1.0 (#3a, #3b), EORTC QLQ-OH15 (#35), Pain NRS at the affected site.
4. Site and timing of oral mucositis onset.
5. Subgroup analysis by chemotherapy regimen for prevention/improvement outcomes.
6. Chemotherapy completion status.
7. Use of concomitant as-needed anti-inflammatory analgesics (from patient diary).
8. Frequency of oral steroid ointment as rescue medication (patient diary).

9. Use of Episil® oral liquid (patient diary).
10. Technical performance assessment.
11. Patient preference for continuation of the investigational device.

#### **Statistical Methods:**

- For items (1)–(2), analyses identical to those for the primary endpoint will be applied.
- For item (5), subgroup analyses by chemotherapy regimen will be performed similarly.
- For other items:
  - Categorical data: same as primary analysis (frequencies, percentages, chi-square).
  - Continuous data: summary statistics (as above), estimation of intergroup differences and 95% CIs, and use of two-sample Wilcoxon or two-sample t-tests depending on distribution.
  - Analyses will also be performed on *change from Day 1*.
  - *Pain NRS* will be analyzed both as a continuous variable and as categorical (0 = none, 1–3 = mild, 4–6 = moderate, 7–10 = severe).
  - For participants with multiple affected sites, the worst score per period will be used.

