### 3. Quality of Life (QOL) Assessment [Patient-Reported Outcomes]

- PRO-CTCAE v1.0 (Items #3a and #3b)
- EORTC QLQ-OH15 (Item #35)
- Pain NRS at affected site

The *Pain NRS* will be derived from the patient diary and represents the maximum pain level during each treatment period.

The scale ranges from **0 to 10**:

- 0: no pain
- 1–3: mild pain
- 4–6: moderate pain
- 7–10: severe pain (10 = “unbearable pain, worst ever experienced”)

4. **Occurrence site and timing of oral mucositis**

Evaluated across all intraoral regions (upper/lower labial vestibule, tongue dorsum/right/left/ventral/tip, buccal mucosa, palate, others), and specifically at the designated affected site.

5. **Subgroup analyses** by chemotherapy regimen for preventive and pain-relieving efficacy.

6. **Chemotherapy completion status** (treatment adherence).

7. **Number of as-needed anti-inflammatory analgesic tablets** (from patient diary).

8. **Number of rescue uses of oral steroid ointment** (from patient diary).

9. **Use of Episil® oral liquid** (presence/absence; patient diary).

10. **Technical performance assessment**

Evaluation of natural, brushing-related, eating-related, and self-induced device dislodgement.

11. **Patient preference for continued use of the investigational treatment**

Evaluation of participants' willingness to continue using the device.

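### Regimen subgroups are to be tested one by one like the primary endpoint, with no test of whether the device effect differs between regimens

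*Protocol*

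**What the plan says.** Section 6(2) lists as secondary endpoint 5 the analyses "by chemotherapy regimen for preventive and pain-relieving efficacy". The rationale at the end of Section 6(2) counts items 5 to 9 as needed to judge the device's efficacy.

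Section 8(2) 3) gives the method. For items 1 and 2, "analyses identical to those for the primary endpoint will be applied". For item 5, "subgroup analyses by chemotherapy regimen will be performed similarly".

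The primary analysis in Section 8(2) 2) consists of a cross-tabulation of grades, responder proportions with 95% CIs, "Comparison between groups using Pearson's chi-square test" at a two-sided 5% level, and "Estimation of the between-group difference with a two-sided 95% CI". Section 8(2) 5) sets 5% two-sided as the general significance level.

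The protocol names no interaction or heterogeneity test for item 5 and no multiplicity control across regimens. Section 7 sizes the trial for the overall comparison only, with rates "conservatively assumed as 50% in the intervention group and 25% in the control group" and 77 participants per group. Section 4(7) stratifies randomization by site, not by regimen.

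**The concern.** The purpose of a regimen analysis is to learn whether the device works better under some regimens than under others. A chi-square test inside each regimen answers a different question: whether that subgroup alone has enough data to reject no effect. Because the trial is powered only as a whole, each part is underpowered. Some parts will then reach significance and others will not, even when the true effect is the same everywhere.

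This is a named secondary endpoint that the protocol ties to efficacy. A list of regimen-specific p-values would invite readers to conclude where the device works and where it does not, on evidence that cannot carry that conclusion.

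**Working it through.** **Inputs from the protocol.** Rates of 50% and 25%, two-sided 5% level, 90% power, Pearson chi-square, 77 per group, 1:1 allocation (Sections 4(7), 7 and 8).

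**Assumed.** The number and size of regimen groups, which the protocol does not give. Near-equal splits of 77 per arm are used: two regimens (39/38 per arm), three (26/26/25) and four (20/19/19/19).

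**Step 1: reproduce the plan's own figure.** With mean rate 0.375,

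n = [1.960 × √(2 × 0.375 × 0.625) + 1.2816 × √(0.5 × 0.5 + 0.25 × 0.75)]² / 0.25²
= [1.960 × 0.6847 + 1.2816 × 0.6614]² / 0.0625 = 76.7, rounded up to 77 per group.

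The stated sample size is reproduced. Exact binomial power of the chi-square test at 77 per arm is 0.906.

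**Step 2: power within each regimen, same effect everywhere (50% v 25%).** Exact binomial enumeration of the uncorrected chi-square test gives:
- 39 and 38 per arm: 0.637 and 0.620
- 26 and 25 per arm: 0.482 and 0.479
- 20 and 19 per arm: 0.375 and 0.384

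(The 20-per-arm value falls slightly below the 19-per-arm value because the test is discrete.)

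**Step 3: chance of a mixed pattern.** P(mixed) = 1 − product of powers − product of (1 − power).

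| Regimens | All significant | None significant | Mixed |
|---|---|---|---|
| Two | 0.395 | 0.138 | 0.467 |
| Three | 0.111 | 0.140 | 0.749 |
| Four | 0.021 | 0.146 | 0.832 |

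**Step 4: sensitivity.**
- Smaller uniform effect (40% v 25%), same splits: mixed in 0.416, 0.516 and 0.543.
- Uneven splits at 50% v 25%: 54/23 gives 0.544, 62/15 gives 0.638, 39/23/15 gives 0.773 and 39/15/12/11 gives 0.842.

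**Step 5: no effect anywhere.** At a common rate of 37.5%, the exact chance of at least one significant regimen is:
- Two: 1 − (1 − 0.0506)(1 − 0.0489) = 0.097
- Three: 0.158
- Four: 0.206

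The nominal values 1 − 0.95ᵏ are 0.098, 0.143 and 0.185.

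**Step 6: the alternative.** In 40,000 simulated trials per setting with a uniform 50% v 25% effect, a 5% heterogeneity test on the risk difference wrongly signalled a regimen difference in 5.4%, 5.8% and 6.9% of trials for two, three and four near-equal regimens. With the uneven four-way split the figure was 7.6%. On the log odds ratio the same four settings gave 4.6%, 3.8%, 3.2% and 2.6%.

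The power of the interaction test is low. With the whole 25-point effect in one of two equal regimens it is 41% on the risk difference and 33% on the odds ratio.

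**The case against.** Several points on the other side have force.

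**No rule equates a mixed pattern with heterogeneity.** A reader might infer that the protocol will declare regimen-specific efficacy from separate p-values. It says no such thing; the error would be one of interpretation. The primary-type analysis also supplies a difference with a 95% CI in each regimen, so part of a sound presentation is already planned. This stands, and it narrows the point to what the tests can support.

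**A mixed pattern in most trials is not established.** That holds across the scenarios computed with three or more regimens, and at 50% v 25% for clearly uneven two-way splits. It fails for two near-equal regimens (47%), and at 40% v 25% it is only just true for three or four. The 14-, 21- and 28-day evaluation points do not prove three sizeable groups, since Section 4(3) makes 21 days the standard.

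**Small cells and lack of stratification.** A reader might add that the chi-square test will break down within regimens. At a mean rate of 0.375, expected counts drop below 5 only at 13 or fewer per arm (0.375 × 13 = 4.9). At 19 per arm the smallest is 7.1. Nor does the absence of stratification by regimen bias the comparison within a regimen, which is still randomized.

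**An analysis plan could add an interaction test.** It could, and the protocol's word for item 5 is looser than the one for items 1 and 2. But its natural reading still prescribes a within-regimen test. The objection is to that stated method, not to missing detail.

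**Conclusion.** The point holds in limited form. The protocol has a named secondary endpoint analysed by unadjusted 5% tests within each regimen, and those tests cannot show that efficacy depends on regimen. Under a uniform design effect they would give a mixed pattern in about 47%, 75% and 83% of trials with two, three and four near-equal regimens, or 42%, 52% and 54% at 40% v 25%. With no effect, at least one regimen would be significant in about 10%, 16% and 21%. An interaction test keeps the false signal of a regimen difference near its nominal 5%.

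These figures rest on assumed numbers and sizes of regimens. The documents support neither an unconditional claim about most trials nor the inference that the protocol itself misreads mixed results. This is an inexpensive improvement to a secondary analysis and does not threaten the trial's main conclusion.

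**What to change.** In Section 8(2) 3), replace the sentence on item 5 so that it:
- keeps the within-regimen proportions and between-group differences with 95% CIs;
- drops the within-regimen chi-square tests as a basis for inference;
- adds one treatment-by-regimen interaction test on the risk-difference scale, which is the scale of the primary estimate;
- requires the regimen groups to be fixed before analysis;
- states that a non-significant interaction will not be reported as proof of a uniform effect.

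The cost is one sentence or two and one extra model. No extra patients, visits or data are needed, since Section 5(1) already records the regimen and its cycle. The price is low power (41% on this scale in the two-regimen case above), so the usual report will be that no difference was shown. With small or uneven groups the test can also run a little above 5%, as the 7.6% above shows.

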## 1. Title

A Multicenter, Randomized, Parallel-Group Confirmatory Study to Evaluate the Efficacy of a Novel Oral Mucosal Protectant (Soft Protector CPC) in Preventing Oral Mucositis and Alleviating Pain in Patients Undergoing Chemotherapy for Breast Cancer

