This confirmatory multicenter randomized controlled trial (four participating institutions) is designed to evaluate the preventive and pain-relieving efficacy of Soft Protector CPC in patients undergoing chemotherapy for breast cancer. Participants will be randomly assigned to receive standard care (oral care  $\pm$  Episil®) with or without the use of Soft Protector CPC. Oral mucositis will be assessed according to CTCAE version 5.0 and version 3.0, which are widely used internationally.

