### **Comparative Period**

- Interview and physical examination.
- Hematology (as above).
- Blood biochemistry (as above).
- Pain and QOL scores (CTCAE v5.0 / v3.0, PRO-CTCAE #3a, 3b, EORTC QLQ-OH15 #35, pain NRS).
- Presence, site, and timing of oral mucositis.
- Presence and timing of oral candidiasis.
- Intraoral photographs.
- Confirmation of concomitant medications/therapies.

- Evaluation of procedural factors.
- Patient preference or acceptability of the investigational treatment.
- ECOG PS.
- Patient diary entries (once daily) including:
  - Device dislodgement (presence/absence),
  - Pain intensity (PRO-CTCAE #3a, #3b; EORTC QLQ-OH15 #35; pain NRS),
  - Number of as-needed anti-inflammatory analgesic tablets,
  - Number of uses of oral steroid ointment as rescue medication,
  - Use of *Episil*® oral liquid (yes/no).
- Adverse events.
- Device malfunctions.
- G-CSF administration (yes/no).

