## **11. Study Background and Scientific Rationale**

This is a multicenter, prospective, open-label, stratified, randomized, parallel-group confirmatory study designed to evaluate the preventive and pain-relieving efficacy of the investigational oral mucosal protectant.

The target sample size was determined to ensure both scientific validity and feasibility within the planned study duration.

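### The trial is confirmatory for alleviating pain, but no pain measure is named to decide it: five secondary pain measures get about ten analyses, each at two-sided 5%

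*Protocol*

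**What the plan says.** **Objective.** The title announces a "Confirmatory Study to Evaluate the Efficacy of a Novel Oral Mucosal Protectant (Soft Protector CPC) in Preventing Oral Mucositis and Alleviating Pain". Section 3 says the trial "is designed to evaluate the preventive and pain-relieving efficacy of Soft Protector CPC", and Section 11 calls it a "confirmatory study designed to evaluate the preventive and pain-relieving efficacy of the investigational oral mucosal protectant".

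**Primary endpoint.** Sections 6(1) and 8(2) 2) name one: "Oral mucositis severity based on CTCAE v3.0 subcriteria during the comparative period". The grade descriptions in Section 6(1) cover erythema, ulceration, pseudomembranes, bleeding and necrosis; pain is not among them. Section 8(2) 2) counts a participant as a success for prevention of onset or for what it labels *pain improvement*. The latter is defined as a drop in this CTCAE v3.0 grade at the target site.

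**Pain measures.** All are secondary. Section 6(2) lists the CTCAE v5.0 oral pain grade and four patient-reported items. Section 5(2) groups those four as "Pain intensity (PRO-CTCAE #3a, #3b; EORTC QLQ-OH15 #35; pain NRS".

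**Analyses.** Under Section 8(2) 3), oral pain is analysed as the primary is. For the other items, categorical data follow "Categorical data: same as primary analysis (frequencies, percentages, chi-square", and continuous data get a Wilcoxon or t-test depending on distribution. Analyses are also made on change from Day 1, and the pain NRS is analysed both as continuous and as categorical.

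**Level.** Section 8(2) 5) gives one statement for the whole analysis: "Significance level: 5% (two-sided". It names no order of testing, no adjustment and no exploratory category. The endpoint rationale in Section 6(2) adds "Items 5–9: necessary to evaluate efficacy of the investigational device", which covers among others analgesic, steroid ointment and Episil use.

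**The concern.** A confirmatory objective needs an endpoint that decides it. For prevention and healing of lesions the primary does this. For pain, the protocol offers a component of the primary that carries the word pain but grades lesions, and then five measures of equal rank that do record pain. If they disagree at the end, nothing says which one answers the question.

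The trial is open-label and four of the five measures are self-reported, so a pain measure chosen after the results are seen would be hard to defend. If one favourable result among many were presented as the pain finding, its error rate would not be the stated 5%.

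**Working it through.** **1. The plan's own figure.** Section 7 gives 50% versus 25%, two-sided 5%, 90% power, Pearson chi-square, 1:1. With mean rate 0.375:

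n = [1.960 × √(2 × 0.375 × 0.625) + 1.282 × √(0.5 × 0.5 + 0.25 × 0.75)]² / 0.25² = (1.342 + 0.848)² / 0.0625 = 76.7, so 77 per group and 154 in total. This matches. Power at 77 per group is 90.1%. The primary is one between-group test at 5%, so its error is controlled.

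**2. Counting the pain analyses (comparative period).**
- CTCAE v5.0 oral pain, analysed as the primary: 1
- PRO-CTCAE #3a, PRO-CTCAE #3b, QLQ-OH15 #35 and pain NRS, as level: 4
- The same four, as change from Day 1: 4
- Pain NRS in its second, categorical form: 1

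That is ten analyses on five measures. The count leaves out the CTCAE v5.0 mucositis grade, which mixes pain with ulceration, as well as the regimen subgroups, the continuous period, and analgesic, steroid and Episil use.

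**3. Chance of at least one false significant result.** With no device effect and k independent tests, the chance in either direction is 1 − 0.95^k: 22.6% for k = 5 and 40.1% for k = 10. In the device's favour it is 1 − 0.975^k: 11.9% and 22.4%.

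Pain measures on the same patient are correlated. The protocol gives no correlation, so a range is assumed. For k standard normal statistics with common correlation ρ, the chance is 1 − P(all |Z| ≤ 1.96) in either direction, and 1 − P(all Z ≤ 1.96) in the device's favour:

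| Assumed ρ | 5 measures, either direction | 5, device's favour | 10 analyses, either direction | 10, device's favour |
|---|---|---|---|---|
| 0.5 | 18.3% | 9.2% | 28.7% | 14.4% |
| 0.7 | 14.8% | 7.4% | 21.3% | 10.7% |
| 0.8 | 12.7% | 6.4% | 17.3% | 8.6% |
| 0.9 | 10.2% | 5.1% | 12.8% | 6.4% |
| Single test | 5% | 2.5% | 5% | 2.5% |

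A common correlation is crude for ten analyses, because level and change of one item are closer to each other than two different items are. A second model doubles all five measures into level and change, with correlation 0.7 or 0.9 within a measure. It gives, in either direction, 25% to 29% at ρ = 0.5 and 14% to 16% at ρ = 0.9. In the device's favour it gives 12% to 15% and 7% to 8%. The picture is the same.

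**4. Cost of the alternatives.** Bonferroni over five measures would test each at 0.01. For an effect of the primary's size at 77 per group, power would be Φ[(0.25 × √77 − 2.576 × 0.685) / 0.661] = Φ(0.65) = 74%. One named measure tested at 5% after the primary avoids that loss on its own test.

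**The case against.** The other side has four points.

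- **The confirmatory test is protected.** There is one primary, one chi-square test and a sample size that reproduces. The pain measures are all labelled secondary. This stands.
- **The primary already contains a pain component.** As written, the protocol looks at pain relief partly through its *pain improvement* category, so it is not correct that the pain objective appears only among the secondaries. What stands is narrower: the component is defined wholly by lesion grade, so a participant can meet it with pain unchanged.
- **Ordering of secondaries often belongs in a statistical analysis plan, which is not shown.** This would answer a protocol that was silent. This one fixes the tests, the repeated analyses and a single level. Which measure decides a stated confirmatory objective is a protocol matter.
- **No decision rule is stated.** A reader might infer that one significant pain result would be taken as proof, even with a failed primary. No passage says so. The statement that items 5–9 are needed to evaluate efficacy explains why endpoints were chosen and is not a claim rule either. The figures above are therefore conditional.

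A reader might also infer that a false pain-relief claim is several times likelier than 5%, or always at least three times the nominal level. The documents do not support this. A false relief claim must favour the device, and that chance is about 5% to 14% over the assumed range. Relative to its own 2.5% benchmark, the multiple runs from about 2 (five measures, ρ = 0.9) to about 6 (ten analyses, ρ = 0.5). With no correlation given, no single multiple can be stated.

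**Conclusion.** The point holds in limited form. Pain relief is part of the confirmatory objective, the primary's pain label rests on a scale without a pain criterion, and five secondary pain measures share about ten analyses at a flat two-sided 5% with none named as decisive. The primary analysis and its sample size are unaffected.

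The size is conditional on two assumptions: that any one significant pain result would be read as showing relief, and that the correlation lies between 0.5 and 0.9. A false result in either direction then has a chance of about 18% to 10% for five measures and 29% to 13% for ten analyses. In the device's favour the chance is about 9% to 5% and 14% to 6%, against 2.5%. This should be corrected before the data are analysed, but it does not threaten the trial's main conclusion.

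**What to change.** In Section 8(2) 3), name one key secondary pain measure with one analysis. An example is the period-maximum pain NRS at the target site in the comparative period, intervention versus control, by one Wilcoxon test, using the worst site where there are several, as the section already provides. State that it is tested at two-sided 5% only if the primary chi-square test is significant. State that all other secondary and subgroup p-values, including the categorical NRS and the change-from-Day-1 versions, are exploratory and reported with estimates and 95% confidence intervals.

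This takes a few sentences and needs no new data or patients. The cost is that the pain claim depends on the primary succeeding, and the other secondaries cannot carry a formal claim.
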